# iTACTIC – implementing Treatment Algorithms for the Correction of Trauma-Induced Coagulopathy: study protocol for a multicentre, randomised controlled trial

**DOI:** 10.1186/s13063-017-2224-9

**Published:** 2017-10-18

**Keywords:** Trauma, Haemorrhage, Trauma-induced coagulopathy, Viscoelastic haemostatic assays, Randomised control trial, Conventional coagulation tests, Transfusion

## Abstract

**Background:**

Traumatic injury is the fourth leading cause of death globally. Half of all trauma deaths are due to bleeding and most of these will occur within 6 h of injury. Haemorrhagic shock following injury has been shown to induce a clotting dysfunction within minutes, and this early trauma-induced coagulopathy (TIC) may exacerbate bleeding and is associated with higher mortality and morbidity. In spite of improved resuscitation strategies over the last decade, current transfusion therapy still fails to correct TIC during ongoing haemorrhage and evidence for the optimal management of bleeding trauma patients is lacking. Recent publications describe increasing the use of Viscoelastic Haemostatic Assays (VHAs) in trauma haemorrhage; however, there is insufficient evidence to support their superiority to conventional coagulation tests (CCTs).

**Methods/design:**

This multicentre, randomised controlled study will compare the haemostatic effect of an evidence-based VHA-guided versus an optimised CCT-guided transfusion algorithm in haemorrhaging trauma patients. A total of 392 adult trauma patients will be enrolled at major trauma centres. Participants will be eligible if they present with clinical signs of haemorrhagic shock, activate the local massive haemorrhage protocol and initiate first blood transfusion. Enrolled patients will be block randomised per centre to either VHA-guided or CCT-guided transfusion therapy in addition to that therapy delivered as part of standard care, until haemostasis is achieved. Patients will be followed until discharge or 28 days. The primary endpoint is the proportion of subjects alive and free of massive transfusion (less than 10 units of red blood cells) at 24 h. Secondary outcomes include the effect of CCT- versus VHA-guided therapy on organ failure, total hospital and intensive care lengths of stay, health care resources needed and mortality. Surviving patients will be asked to complete a quality of life questionnaire (EuroQol EQ-5D^TM^) at day 90.

**Discussion:**

CCTs have traditionally been used to detect TIC and monitor response to treatment in traumatic major haemorrhage. The use of VHAs is increasing, but limited evidence exists to support the superiority of these technologies (or comparatively) for patient-centred outcomes. This knowledge gap will be addressed by this trial.

**Trial registration:**

ClinicalTrials.gov, ID: NCT02593877. Registered on 15 October 2015.

**Electronic supplementary material:**

The online version of this article (doi:10.1186/s13063-017-2224-9) contains supplementary material, which is available to authorized users.

## Background

Traumatic injury is responsible for a large and increasing proportion of the world’s burden of disease and is the fourth leading cause of death globally [1]. Half of all trauma deaths are due to bleeding and most of these will occur within 6 h from injury [2]. Haemorrhagic shock following injury has been shown to induce a clotting dysfunction (i.e. coagulopathy) within minutes [3–5]. Such early trauma-induced coagulopathy (TIC) may exacerbate bleeding and is associated with higher mortality and morbidity [4, 6, 7]. Many more injured patients will go on to develop different types of coagulopathy at different times during the course of their treatment, either as a result of their body’s ongoing response to trauma or as a consequence of their clinical care. Coagulopathic, haemorrhaging trauma patients have increased blood transfusion requirements, increased mortality and more adverse outcomes [8]. Despite improvements in surgical techniques, resuscitation strategies and intensive care treatments, outcomes for critically injured patients remain poor [9]. Within the last decade research focussing on TIC has led to improved resuscitation strategies, resulting in the early and more aggressive use of blood products and coagulation factors for the management of massively bleeding patients.

In spite of improved resuscitation strategies, current transfusion therapy still fails to correct coagulopathy during ongoing haemorrhage [10, 11]. The mechanisms and genesis of TIC have yet to be fully elucidated, and there are many questions about how to optimally diagnose, resuscitate and monitor the critically bleeding trauma patient. It is important to detect TIC as early as possible. Conventional coagulation tests (CCT), such as prothrombin time/international normalised ratio (PT/INR), activated partial thromboplastin time (APTT), fibrinogen concentration and PLT, have traditionally been used. However, there is a striking lack of evidence to support the use of these CCTs to monitor resuscitation, although threshold triggers for intervention based on CCTs have been suggested [5]. Recent published evidence describes an increasing recognition for the potential of the two current market-leading Viscoelastic Haemostatic Assays (VHAs) namely thromboelastography (TEG®; Haemonetics Incorporation) and rotational thromboelastometry (ROTEM®; TEM Innovation GmbH). Both platforms use similar test modes to rapidly and accurately determine the functional coagulation status of patient whole blood. However, the evidence base supporting a role for these VHA devices is limited, and less attention has been directed to understanding their cost-effectiveness. Cost-effectiveness may be particularly relevant both in the context of additional therapeutic interventions required, but also in potential savings, if fewer treatments are required based on delivery of individualised assessments of haemostasis.

The relative contribution of blood components, such as fibrinogen and platelets, to clot strength can be evaluated through the use of specific inhibitors or agonists [12]. The viscoelastic properties of blood samples are recorded under low shear conditions, thereby providing a comprehensive visual profile of clot formation and breakdown (fibrinolysis).

Unlike laboratory-based CCTs which might take more than 60 min for the results to be available to clinicians [8], VHA is a point-of-care device which might provide clinically relevant results within even 5–10 min and thus may be repeated in a massive bleeding situation to identify patient-specific needs for transfusion components in a timelier manner. Furthermore, VHAs provide the potential to detect hyperfibrinolysis, and possibly hypercoagulability. However, VHA assays and testing have costs, require training and additional oversight, and may not provide insight into other potentially important haemostatic derangements at the endothelial or platelet level. In addition, other publications attest to how changes in the process and pathways for the delivery of CCTs can be modified and accelerated [13, 14].

Whilst VHA has been used for many years in liver transplant and cardio-pulmonary surgery, robust data supporting its universal uptake in the context of trauma are lacking. Whilst some publications have attempted to identify VHA patterns and thresholds characterizing TIC and the need for massive transfusion in trauma patients, definitive evidence proving its superiority over CCTs in the diagnosis and management of coagulopathy in the acute setting is not available [15–18].

Although considered a preventable major cause of death, the management of coagulopathic bleeding in trauma patients remains primarily based upon retrospective registry studies of survival and extrapolating the results of transfusion practice performed in the elective, non-acute surgical setting. Treatment is diverse comprising the empiric transfusion of red blood cells (RBC) and clotting product supplements to patients, blind to the type and severity of TIC they may have – or indeed even if they do not have coagulopathy. It is well established that blood transfusion carries significant health risks both related to transmission of pathogens and to the development of transfusion reactions. Published in 2015, the results of the Pragmatic, Randomised Optimal Platelet and Plasma Ratios (PROPPR) trial [19] provide the best evidence to date for optimal trauma haemorrhage resuscitation. PROPPR demonstrated that an empiric massive transfusion protocol (MTP) aiming at a ratio of 1:1:1 of blood components (RBC 1: plasma 1: platelets 1) administered from the early phase of care and during ongoing haemorrhage was associated with fewer exsanguinations in the initial 24 h (*p* = 0.03) and a tendency towards improved 24-h survival (*p* = 0.12) than a 1:1:2 ratio.

The present prospective randomised controlled trial (RCT) will employ evidence-based treatment algorithms to compare outcomes of VHA-guided resuscitation versus CCT resuscitation support in haemorrhaging trauma patients.

The hypothesis for this comparative study is that VHA-directed therapy will enhance early haemostatic control by the targeted correction of TIC, whilst also reducing the total amount of blood products and procoagulants administered to all bleeding trauma patients, including those not having TIC. This would significantly reduce both the number of patients receiving blood transfusion and the number of transfused blood products per transfused patient, thereby improving both patient safety and resource utilisation.

## Methods/design

This is an investigator-initiated, multi-centred, superiority, parallel-group, randomised controlled trial performed at eight major trauma centres. The trial sites include: Rigshospitalet (Copenhagen, Denmark), Academic Medical Centre (Amsterdam, The Netherlands), Oslo University Hospital (Oslo, Norway), Kliniken der Stadt Köln gGmbH Cologne, Germany), The Royal London Hospital (London, UK), John Radcliffe Hospital (Oxford, UK). Nottingham University Hospitals, Queen’s Medical Centre (Nottingham, United Kingdom) and University of Kansas Hospital (UKH) (Kansas City, MO, USA) are planning to start recruitment in 2017.

This protocol (Additional file 1) conforms to the Consolidated Standard of Reporting Trials (CONSORT) guidelines. Figure 1 shows the Standard Protocol Items: Recommendation for Interventional Trials (SPIRIT) schedule of enrolment, interventions and assessments. The SPIRIT Checklist is given in the Additional file 2.

**Fig. 1 Fig1:**
[figure not shown]
Standard Protocol Items: Recommendation for Interventional Trials (SPIRIT) schedule of enrolment, interventions and assessments

An overview of the study process is provided in Fig. 2 (study scheme).

**Fig. 2 Fig2:**
[figure not shown]
Study scheme

### Inclusion criteria

Adult trauma patients (according to local definitions) will be enrolled if they present with clinical signs of haemorrhagic shock, according to the responsible trauma team leader, activate the local massive haemorrhage protocol, according to the participating institutions’ specific routines, and initiate first transfusion. Participants must be randomised within 3 h of injury and 1 h of admission to the ED of the participating study site. Agreement is provided on behalf of incapacitated patients by a personal consultee (PC) or a nominated consultee (NC).

### Exclusion criteria

There are no exclusion criteria.

### Primary objective

The primary objective is to compare the haemostatic effect of VHA assay-guided transfusion strategy versus optimised CCT-guided transfusion strategy in haemorrhaging trauma patients.

### Secondary objective

The secondary objectives of the study are to determine the effects of VHA-led versus optimised CCT-guided resuscitation on organ failure, hospital length of stay (LOS), intensive care unit (ICU) stay, duration of mechanical ventilation, health care resource needs and mortality.

### Primary endpoint

The primary endpoint is the proportion of subjects alive and free of massive transfusion (less than 10 units of RBC transfused) at 24 h post admission.

### Secondary endpoints

The secondary endpoints listed below will be analysed in order to provide a sensitive and comprehensive description of outcomes and health care resource demands for the VHA and CCT arm subjects:All-cause mortality at 6 and 24 h and 28 and 90 days post admissionDuration and severity of coagulopathy until haemostasis, as defined by the area under the time multiplied by Prothrombin Ratio (PTr) curve, with coagulopathy defined as PTr > 1.2. Patients who die will have their time of haemostasis set at 24 h, and last PTr extrapolated to this time pointProportion of patients who have corrected coagulopathy, defined as PTr < 1.2, after first 8 units of RBCTime to haemostasis (defined as having occurred at the end of the first hour free of red cell transfusions and the treating clinicians believe primary haemostasis has been achieved)Time spent in coagulopathic condition, defined as PTr ≥ 1.2, until haemostasis, defined as the point 1 h from the last administration of RBC and the treating clinician believes that primary haemostasis has been achievedBlood products administered (RBC, plasma, platelets alone and in total) within first 6 and 24 h after admission28-day ventilator-free and ICU-free days (patients who die in hospital during the 28-day study period will be considered to have zero hospital-free days)Total hospital length of stay28-day symptomatic thromboembolic events defined as: deep venous thrombosis (DVT) diagnosed by compression ultrasound or venography, pulmonary embolism diagnosed by computed tomography (CT) pulmonary angiogram or ventilation-perfusion scan or myocardial infarction and/or stroke identified by standard clinical diagnostic investigation(s)Incidence of transfusion-related complicationsIncidence of organ dysfunction, defined by Sequential Organ Failure Assessment (SOFA) scoreHealth care resource, productivity costs and HRQoL (EuroQol EQ-5DTM at discharge or day 28, and at day 90)Lifetime health economic cost-effectiveness of personalised VHA-guided haemorrhagic treatment versus MTP-based on best practice and CCTs

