### Initiation of study care

Corresponding and optimised algorithms based on VHA trigger parameters for the VHA arm and CCT results for the CCT arm, respectively, have been developed and will be applied in the enrolled subjects (Fig. 3a, b, c). During active haemorrhage, samples will be taken for CCT/VHA analysis at baseline and after every 4 units of RBC until haemostasis. The results from each blood sample will be acted upon as soon as they are available. For the VHA arm, this implies acting upon the parameters as they are appearing, not waiting until the VHA trace is completed.

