### Randomised study care – VHA arm

VHA will be conducted for all subjects in the VHA arm at each time point up to 24 h. During active haemorrhage, samples will be taken for VHA analysis at baseline and after every 4 units of RBC until haemostasis. The clinical course of subjects randomised to the VHA arm will follow a treatment algorithm utilizing VHA results (Fig. 3a and b). The subject will be treated with standard haemostatic resuscitation based on a MTP aiming for 1:1:1 ratio of blood components and initial TXA. In addition, according to threshold values in the algorithms, the subjects will be given fibrinogen concentrate or cryoprecipitate and/or additional platelets, plasma and TXA depending on the VHA results.

Fibrinogen concentrate or cryoprecipitate will be administrated when FIBTEM Clot Amplitude at 5 min (CA5) is below 10 mm or functional fibrinogen (FF) TEG® Maximum Amplitude (MA) is below 20 mm. Additional platelets are indicated when the subtracted amplitude of FIBTEM CA5 from EXTEM CA5 is below 30 mm, or the subtracted amplitude of FF TEG® MA from rapid TEG® MA is below 45 mm. Additional plasma is indicated when the results show a normal EXTEM CA5, defined as above 40 mm, but still a prolonged EXTEM clotting time (CT), defined as above 80 s, or normal rapid TEG® MA, defined as above 65 mm, but still a prolonged rapid TEG® activated clotting time (ACT), defined as above 120 s. Additional TXA is indicated when the EXTEM Lysis Index at 30 min (LI30) is below 85% or rapid TEG® clot lysis at 30 min (Ly30) is above 10%.

This VHA treatment algorithm is based upon analysis of more than 2200 trauma subjects enrolled to a prospective observational study conducted at the participating study sites, entitled Activation of Coagulation and Inflammation in Trauma (ACIT). Analysis of the ACIT dataset has enabled the definition of clinically relevant VHA thresholds and patterns by which it is possible to rapidly identify coagulopathic patients and anticipate the need for massive transfusion. These threshold parameters have been applied to the generation of an evidence-based targeted treatment algorithm.

According to pre-designation, each study centre will only conduct VHA using either thromboelastography (TEG®) or rotational thromboelastometry (ROTEM®) to determine the following parameters:TEG®: RapidTEG® ACT, MA and Ly30; functional fibrinogen TEG® MAROTEM®: EXTEM CT, CA5 and Li30; FIBTEM CA5

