### Randomised study care – CCT arm

CCTs will be conducted for all subjects in the CCT arm at each time point up to 24 h. The tests will comprise platelet counts (PLT), activated partial thromboplastin time (aPTT), prothrombin time – international normalised ratio (PT/INR) and Clauss fibrinogen assay. PTr and Clauss fibrinogen will be measured for all study subjects at each time point.

The clinical course of subjects randomised to the CCT arm will follow a treatment algorithm utilizing CCT results (Fig. 3c) and based upon current published evidence and empiric best practice according to the PROPPR and CRASH-2 trials data (i.e. a 1:1:1 product ratio, with the anti-fibrinolytic TXA) [19–21]. The subject will be treated with standard haemostatic resuscitation based on a MTP aiming for a 1:1:1 ratio of blood components and initial TXA. In addition, the subjects will be given fibrinogen concentrate or cryoprecipitate and/or additional platelets and plasma depending on the CCT results.

Fibrinogen concentrate or cryoprecipitate will be indicated when fibrinogen values are below 2.0 g/L. Additional platelets will be indicated with PLT below 100 × 10^9^/L and additional plasma will be administrated when the INR is above 1.2 despite normal fibrinogen, defined as 2.0 g/L or above. There are no generally accepted indications for additional anti-fibrinolytic therapy using CCTs.

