### Cessation of study care (haemostasis)

For the purposes of this comparative study, haemostasis (end of study care) will be defined as the point 1 h from the last administration of RBC and the treating clinician believes that primary haemostasis has been achieved.

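### The PTr-area endpoint scores deaths to 24 h but sets no 24 h limit for survivors, so a survivor with late haemostasis can score worse than a patient who died

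*Protocol article*

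**What the plan says.** The rule for deaths is in the protocol article under Secondary endpoints, in the item on duration and severity of coagulopathy: "Patients who die will have their time of haemostasis set at 24 h". The same sentence carries the last PTr forward to that time. It is attached to this item only.

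For survivors the area runs to haemostasis. Cessation of study care says that "haemostasis (end of study care) will be defined as the point 1 h from the last administration of RBC", together with the clinician's judgement. The separate time-to-haemostasis item uses a slightly different definition, "defined as having occurred at the end of the first hour free of red cell transfusions". Neither has an upper limit in hours. A third item, "Time spent in coagulopathic condition, defined as PTr ≥ 1.2, until haemostasis", also runs to haemostasis, with no limit and no rule for deaths.

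The measurement horizon is described in two ways. Initiation of study care states that "samples will be taken for CCT/VHA analysis at baseline and after every 4 units of RBC until haemostasis". The two arm sections state that "VHA will be conducted for all subjects in the VHA arm at each time point up to 24 h" and "CCTs will be conducted for all subjects in the CCT arm at each time point up to 24 h". The VHA arm section also repeats the rule of sampling until haemostasis. The CCT arm section adds that "PTr and Clauss fibrinogen will be measured for all study subjects at each time point".

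**The concern.** The time axis is closed at 24 h for patients who die and open for patients who live. With PTr held equal and above the counting baseline, a patient still being transfused on the second day collects more area than one who bled to death on the first. An arm that keeps severe bleeders alive past 24 h could then look worse for that reason on an endpoint meant to show better control of coagulopathy. The background hypothesis is early haemostatic control through targeted correction of coagulopathy, and this endpoint bears directly on it.

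There is also a data question. If PTr testing stops at 24 h, the later part of a survivor's curve has no planned measurements, and the carry-forward rule is written for deaths only. Two analysts could follow the article and obtain different values for the same patient. The coagulopathic-time endpoint has the same gap.

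**Working it through.** The article gives no computed figure for this endpoint, so there is none to reproduce. The check applies the scoring rule to example patients.

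**Inputs from the article:** deaths are scored to 24 h with last PTr carried forward; survivors are scored to haemostasis without limit; coagulopathy is PTr above 1.2.

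**Assumptions for illustration:** PTr is constant over the scored period, deaths have a last PTr of 1.5 or 2.0, survivors have a PTr of 1.3 or 1.5, and late haemostasis falls at 25 or 30 h. The article gives no such values.

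**Formulas.** The wording allows the area to be counted from zero or above the 1.2 threshold, so both are shown:
- from zero: PTr × t
- above 1.2: max(0, PTr − 1.2) × t

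| Patient | PTr | Hours scored | Area from zero | Area above 1.2 |
|---|---|---|---|---|
| Death | 1.5 | 24 | 1.5 × 24 = 36.0 | 0.3 × 24 = 7.2 |
| Survivor | 1.5 | 30 | 1.5 × 30 = 45.0 | 0.3 × 30 = 9.0 |
| Survivor | 1.3 | 30 | 1.3 × 30 = 39.0 | 0.1 × 30 = 3.0 |
| Survivor | 1.3 | 25 | 1.3 × 25 = 32.5 | 0.1 × 25 = 2.5 |

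The first survivor scores worse than the death on both counts, through time alone. The second scores worse from zero but better above 1.2. The third scores better on both.

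**Break-even PTr for a survivor at time t:**
- from zero: PTr of the death × 24 / t
- above 1.2: 1.2 + (PTr of the death − 1.2) × 24 / t

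At t = 30 h:
- against a death at 1.5: 1.5 × 24/30 = 1.20 from zero, and 1.2 + 0.3 × 24/30 = 1.44 above 1.2
- against a death at 2.0: 2.0 × 24/30 = 1.60 from zero, and 1.2 + 0.8 × 24/30 = 1.84 above 1.2

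A survivor at 30 h scores worse than the death when the survivor's mean PTr is higher than these values.

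**With survivors also stopped at 24 h:** a survivor at PTr 1.5 scores 36.0 or 7.2, the same as the death. A survivor can then exceed a death only through a higher PTr, not through a longer time.

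**The case against.** The strongest reply is that a 24 h horizon is already implied. Both arm sections end testing at 24 h, deaths are set to 24 h, and the primary endpoint and the longest blood-product window are also 24 h. A sensible analyst might stop every curve there. That reading is plausible, but no sentence says that the area or the time of haemostasis is truncated, and sampling until haemostasis is stated beside it. The two readings also lead to different problems. If tests end at 24 h, later area has no planned data. If sampling continues to haemostasis, the data exist and the open time axis takes full effect. The article does not settle which applies, so it would be wrong to assert that PTr is unmeasured after 24 h.

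A reader might infer that every survivor with haemostasis after 24 h scores worse than a death. The rule does not support this: the endpoint is an area, and the survivor at PTr 1.3 and 25 h scores better on both counts. At a PTr of 1.2 or below, area above 1.2 is zero whatever the time.

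A reader might also infer a large loss of precision. One simulation assumes 12% deaths at PTr 1.5, early survivors with median haemostasis at 3 h (lognormal, log-SD 0.6) and PTr 1.2, and 2% to 10% of survivors with haemostasis spread over 24 to 72 h at PTr 1.15. Counted from zero, the untruncated variance is 1.30 to 2.20 times the truncated one, an effective sample size loss of 1 − 1/1.30 = 23% to 1 − 1/2.20 = 55%. With the same inputs counted above 1.2, the ratio is exactly 1.0. With late survivors at PTr 1.3 it is 1.05 to 1.21. The share of late survivors has no source in the article, so no such loss can be claimed.

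It is also fair to say that truncation details are often left to an analysis plan. The point stands because the article itself fixes a scoring rule for one group of patients, and that rule, followed literally, can reverse the intended order.

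**Conclusion.** The point holds in a limited form. The PTr-area endpoint scores deaths to 24 h and states no limit for survivors, so a survivor with haemostasis after 24 h and a PTr similar to that of a death, above 1.2, gets the larger area. In the worked example this is 45.0 against 36.0 from zero, or 9.0 against 7.2 above 1.2, assuming constant PTr of 1.5 and haemostasis at 30 h. It can happen but need not.

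The effect on the trial's results cannot be computed, because the article gives neither the number of survivors with haemostasis after 24 h nor their PTr values. It may be small. The death rule applies to the area endpoint alone, so the reversal of order does not arise, as written, for time to haemostasis or coagulopathic time. Coagulopathic time shares only the unclear horizon. The primary endpoint and the sample size are unaffected.

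**What to change.** State under Secondary endpoints that the PTr area and the time in coagulopathic condition are evaluated over one common 24 h analysis window for survivors and deaths, and that survivors not yet at haemostasis are truncated at 24 h. Reconcile the wording on how long samples are taken in Initiation of study care and in the two arm sections. The samples also guide treatment, so this should clarify the text without changing study care.

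The cost is a sentence of endpoint wording and some editing, with no new data. There are two downsides. Haemostasis times beyond 24 h are no longer distinguished in these two endpoints. Late survivors also tie with deaths on time, so death is not made strictly the worst outcome, and a survivor with a higher PTr can still score above a death. What is removed is the reversal caused by time alone.

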#### Randomisation procedure

Enrolled patients will be block randomised per centre to either the CCT or the VHA study arm within 3 h of injury and within 1 h of admission. The trial will be un-blinded for clinical staff and site investigators. Once a patient is determined eligible for the study and informed consent or agreement has been obtained, each subject will be enrolled as soon as possible and will be assigned a unique alphanumeric study identifier. Randomisation will be performed by the site investigator opening a sealed envelope containing the randomised treatment group, to allow for immediate allocation of subjects. An independent party, appointed by the sponsor, will generate the randomisation sequence and site envelopes centrally.

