#### Blood products and procoagulants

Timings, total number (and doses if appropriate) of different blood products and procoagulants administered both pre-hospital and after admission to the study centre, during resuscitation and after 6 and 24 h will be recorded including:RBC, fresh frozen plasma (FFP)/Octaplas, cryoprecipitate, platelets, whole blood and/or autologous RBC from cell salvageCoagulation factor concentrates (prothrombin complex concentrate (PCC), fibrinogen, activated recombinant factor VII (rFVIIa))TXA

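### Time to haemostasis, and two endpoints that end at it, depend partly on the belief of un-blinded clinicians who see the assigned test; an analysis based on red cell timings alone should stand beside them

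*Protocol article*

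**What the plan says.** The protocol article, under Secondary endpoints, dates time to haemostasis at "the end of the first hour free of red cell transfusions and the treating clinicians believe primary haemostasis has been achieved". For the end of study care, the section Cessation of study care uses "the point 1 h from the last administration of RBC and the treating clinician believes that primary haemostasis has been achieved". Near-identical wording closes the time spent in a coagulopathic condition (Secondary endpoints) and defines initial haemostasis under Bleeding episodes. The area under the prothrombin ratio (PTr) curve also runs until haemostasis, with patients who die assigned 24 h.

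Every one of these definitions joins two conditions: an hour without red blood cells (RBC), and the treating clinician's belief. The article gives no criteria for that belief and mentions no blinded assessment of it.

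On who holds the belief, Randomisation procedure states: "The trial will be un-blinded for clinical staff and site investigators". On what they see, Initiation of study care states: "The results from each blood sample will be acted upon as soon as they are available". On result speed, the Background says that "VHA is a point-of-care device which might provide clinically relevant results within even 5–10 min", against "laboratory-based CCTs which might take more than 60 min for the results to be available to clinicians".

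The primary endpoint is being alive with fewer than 10 RBC units at 24 h after admission. It makes no reference to haemostasis or to belief.

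**The concern.** A required component of the endpoint is a judgement by people who know the arm and whose information differs between arms in content and possibly in speed. If knowledge of the arm, or the arrival of a result, influences when or whether they declare haemostasis, the arms can differ on these endpoints although bleeding stopped at the same moment.

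At stake is the interpretation of three secondary endpoints: time to haemostasis, the PTr area and time in coagulopathic condition. Time to haemostasis is the most direct measure of the hypothesis that VHA guidance enhances early haemostatic control. A difference favouring VHA could not be separated, from the planned endpoints alone, from a difference in how haemostasis was declared.

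This is separate from the fact that the article uses two wordings, the first RBC-free hour and one hour from the last RBC. It would remain under a single wording.

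**Working it through.** The plan states no figure for haemostasis time, so there is none to reproduce. Two routes can be worked through.

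**Route 1: belief decides which RBC-free hour counts.** Take a patient who receives a unit at time A, then none for more than an hour, then a last unit at time B.
- Under the first-hour wording, if the clinicians believe haemostasis was reached in the gap, the time is A + 60 min.
- If they do not, the time is B + 60 min.
- The difference is B − A, which exceeds 60 min by construction.

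The transfusion record is the same in both cases. The later unit is also classified differently: as a possible new bleeding episode after initial haemostasis, or as part of continued bleeding. Either judgement may be clinically right. The point is that the person making it knows the arm.

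**Route 2: belief waits for a result.** Inputs:
- RBC-free hour, required in both arms: 60 min (Secondary endpoints).
- VHA result: 5–10 min (Background).
- CCT result: possibly more than 60 min, no upper figure (Background). The values of 75, 90 and 120 min below are assumptions.
- s = minutes from the last RBC to the sample waited for (negative if drawn before it). This is not given in the article, and is assumed equal in both arms.

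If belief is formed when the result arrives, and the time of belief is what is recorded:

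earliest haemostasis after last RBC = max(60, s + turnaround)

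difference between arms = max(60, s + CCT) − max(60, s + VHA)

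| s (min) | CCT (min) | VHA (min) | CCT arm | VHA arm | Difference (min) |
|---|---|---|---|---|---|
| −30 | 60 | 5–10 | 60 | 60 | 0 |
| −30 | 90 | 5–10 | 60 | 60 | 0 |
| −30 | 120 | 5–10 | 90 | 60 | 30 |
| 0 | 60 | 5–10 | 60 | 60 | 0 |
| 0 | 75 | 5–10 | 75 | 60 | 15 |
| 0 | 90 | 5–10 | 90 | 60 | 30 |
| 0 | 120 | 5–10 | 120 | 60 | 60 |
| 30 | 60 | 10 | 90 | 60 | 30 |
| 50 | 60 | 10 | 110 | 60 | 50 |
| 55 | 60 | 5 | 115 | 60 | 55 |

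The RBC-free hour is a floor in both arms. It absorbs the whole turnaround difference when the sample is drawn at or before the last RBC and the CCT result is back within 60 min. The full 50–55 min (60 − 10 and 60 − 5) appears only when a sample is drawn late in the RBC-free hour.

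Whether such samples exist is uncertain. The trigger during active haemorrhage (baseline and every 4 RBC units, Initiation of study care) yields none within an RBC-free hour. The two sections on randomised study care also require tests at each time point up to 24 h, but the schedule is in a figure that is not shown.

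The share of patients in whom belief waits for a result is not given, so no mean shift can be stated.

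**The case against.** The strongest case against has five parts.

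- **The time stamp may be anchored to RBC.** Both wordings date haemostasis by the RBC record. Belief can be read as a condition for that point to count, with no clock of its own. On that reading Route 2 adds no minutes. This stands as a possible reading; Route 1 is unaffected by it under the first-hour wording.
- **The 60-minute figure is not this trial's turnaround.** It is a background remark, hedged, and the same section notes that CCT delivery can be modified and accelerated. The comparator is described as optimised. This stands, and is why the minutes above are assumptions.
- **No text says belief rests on the coagulation result.** This stands. The documents show only that clinicians see and act on the assigned test. Knowledge of the arm, however, is enough for arm-dependent declaration without any waiting.
- **The coagulopathy endpoints are largely objective.** PTr is a laboratory value measured in both arms, and deaths are fixed at 24 h in the area endpoint. This stands: only the cut-off carries the judgement.
- **An RBC-only time is not free of bias.** The same un-blinded staff decide when RBC are given, and a pause in transfusion during continued bleeding would count as haemostasis, which the belief condition guards against. This stands, and argues against replacing the clinical definition.

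The unseen analysis plan may hold a sensitivity analysis. The definition itself is fixed in the article, so the weakness does not depend on that.

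**Conclusion.** The three haemostasis-based secondary endpoints are open to arm-dependent declaration, because belief by un-blinded clinicians can select the qualifying RBC-free hour or delay the declaration. It cannot bring haemostasis before the end of an RBC-free hour.

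The size is not determined by the documents. From result speed alone, and only if belief waits for the result and the time of belief is what is recorded, it is 0 min when the last sample is drawn at or before the last RBC and CCT is back within 60 min. It reaches about 50–55 min when a sample is drawn late in the RBC-free hour, and can be larger if CCT takes longer than 60 min. Selection of a different RBC-free hour can move an individual time by more than 60 min. How often either happens is unknown.

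Two stronger readings are not supported. A reader might infer that VHA's speed builds in a 50–55 min advantage for each patient who waits; that subtraction ignores the RBC-free hour required in both arms. A reader might also infer that the primary comparison is affected; its definition contains no belief component.

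**What to change.** Keep the stated clinical definition, both as the end of study care and for the endpoints. For time to haemostasis, the PTr area and time in coagulopathic condition, pre-specify a sensitivity analysis in which haemostasis time is derived from RBC time stamps alone, under one fixed RBC-free-interval rule. Report it beside the belief-based result, and claim faster haemostasis only if the two agree in direction.

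Because the article words the interval in two ways, those passages must be reconciled before the rule is fixed; which wording to adopt is for the investigators.

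The cost is analysis wording and programming. The data are already to be collected: the section Blood products and procoagulants lists "Timings, total number (and doses if appropriate) of different blood products and procoagulants administered".

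The downsides should be stated with the result. The RBC-only time can count a pause in transfusion during continued bleeding as haemostasis. It can be lengthened by a late unit given for other reasons. It does not remove bias from RBC decisions taken by un-blinded staff. What it does show is whether a difference between arms depends on the declared belief.
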